## 1. Rationale

### 1.a. Statement of the Problem

Post-traumatic stress disorder (PTSD) is a common psychiatric disorder that can be precipitated by severe psychological trauma including combat, accidents, and physical or sexual assault. Left untreated, PTSD can become a chronic, disabling condition associated with significant depression, aggression, family disruption, and substance abuse (Bremner et al., 1996). There is accumulating evidence that PTSD is also associated with increased morbidity and mortality from cardiovascular disease, suicide, and other illnesses (Bell and Nye, 2007; Boscarino, 2008; Jakupcak et al., 2009). Given the high cost of this disorder to veterans, their families, and society at large, improving its treatment is a high priority within the Department of Veterans Affairs (VA).

In a VA-commissioned review of the state of treatment of PTSD, the Institute of Medicine (IOM) did not find evidence to support the efficacy of commonly used psychotropic medications (IOM, 2008). This is of particular concern since pharmacotherapy is a major treatment modality for PTSD in the VA. Among veterans who initiate PTSD treatment at the VA, 50% are prescribed psychotropic medication within the first year (Spoont et al., 2010); among veterans in chronic care for PTSD, 80% are receiving psychotropic medications (Mohamed and Rosenheck, 2008). The vast majority are prescribed an antidepressant, primarily selective serotonin reuptake inhibitors (SSRIs). However, controlled trials have not found SSRIs to be effective in PTSD (Hertzberg et al., 2000; Friedman et al., 2007). In a 12 week placebo-controlled trial of sertraline in veterans, active treatment was not associated with improvements in PTSD, its associated symptoms (depression, anxiety, sleep disturbance), or quality of life (Friedman et al., 2007). Antipsychotics, mood-stabilizers, sedatives, and hypnotics are also widely used, alone and in combinations, despite limited efficacy data and some concerns regarding safety (e.g., metabolic and neurologic side effects). The extensive use of polypharmacy, incorporating off-label medications and medications that have not been shown to be effective, highlights the limitations in the current psychopharmacological approach to PTSD. There is clearly a need to develop more effective pharmacological treatments. Whereas the medications that are widely used to treat PTSD were developed for use in other disorders and are prescribed for long-term use, medication strategies that specifically target PTSD symptoms and/or pathophysiology may be more effective and possibly even curative. Therefore, we propose to examine whether targeting hypothalamic-pituitary-adrenal (HPA) axis dysregulation in PTSD with mifepristone – which recalibrates the HPA axis through peripheral and central mechanisms – will be of therapeutic benefit.

Decades of work by VA investigators and others have demonstrated that dysregulation of the HPA axis is a feature of PTSD pathophysiology and an important potential biological treatment target. The neuroendocrine profile in PTSD is a unique one, best characterized by increased levels of corticotrophin-releasing hormone (CRH) (Bremner et al., 1997; Baker et al., 1999) and enhanced sensitivity to exogenous glucocorticoids in some, but not all, target tissue in the absence of hypercortisolism. Indeed, despite the activation of CRH pathways, 24 hour urinary and plasma cortisol levels are often found to be low in PTSD (Kanter et al., 2001; [name], 2002). Numerous studies in veterans and civilians have demonstrated enhanced suppression of cortisol by the synthetic glucocorticoid dexamethasone (DEX) in PTSD (e.g., [name] et al., 1993; [name] et al., 2002; Newport et al., 2004), which appears to reflect enhanced glucocorticoid receptor (GR) sensitivity at the level of the pituitary. A prospective study examining GR number in lymphocytes before deployment found that a greater number of GR predicted PTSD to combat trauma, thus providing support for the view that GR alterations are risk factors for PTSD (van Zuiden et al., 2011). What is unknown is whether the observed GR alterations in multiple target tissues represent a primary alteration or a secondary adaptation to disturbances in other aspects of HPA axis activity.

One hypothesis is that the up-regulation of glucocorticoid receptors in PTSD and increased sensitivity to dexamethasone are secondary adaptations attempting to normalize inadequate glucocorticoid signaling (Raison and Miller, 2003). Low cortisol has been described in the initial aftermath to trauma in some trauma survivors who go on to develop PTSD and is often observed in those with chronic PTSD ([name] 2002). An inadequate cortisol response at the time of trauma or in its aftermath may lead to a failure to constrain stress

responsive systems following stress exposure leading to the cascade of neurobiological events associated with PTSD. Since low cortisol is not an invariable feature of the disorder it is important to consider that inadequate cortisol signaling in PTSD can also be inferred by consideration of the target tissues that are regulated by glucocorticoids (Raison and Miler et al., 2003). Glucocorticoids are known to mobilize immune responses during stress, restrain the sympathetic nervous system and inhibit CRH activity in the hypothalamus. In PTSD there is consistent evidence of enhanced sympathetic nervous system (SNS) leading to increased catecholamine levels (Kosten et al., 1987; Southwick et al., 1997), increased activity of CRH pathways (Bremner et al., 1997; Baker et al., 1999), immune activation and a shift toward a pro-inflammatory cytokine profile (Raison and Miller, 2003; von Känel et al., 2007). These neurobiological markers have been consistently described in PTSD could be explained by inadequate glucocorticoid signaling. These neurobiological makers are believed to contribute to the behavioral, metabolic, and immune alterations associated with this disorder (Raison and Miller, 2003). Thus, it is important to determine whether recalibrating a dysregulated HPA axis and enhancing glucocorticoid signaling pathways is of therapeutic benefit in PTSD.

Mifepristone is of particular interest for development in PTSD because it is a glucocorticoid receptor antagonist that is hypothesized to recalibrate the HPA axis through blockade of peripheral and central GR and enhance central glucocorticoid signaling (Belanoff et al., 2002; Karssen et al., 2003; Buckley et al., 2008). Peripheral GR blockade results in increased cortisol and adrenocorticotropin hormone (ACTH) levels owing to blockade of cortisol's feedback inhibition of the HPA axis. At high doses mifepristone also has central effects. It crosses the blood-brain barrier, as evidenced by animal studies that demonstrate that there are comparable levels of drug in both plasma and brain after a peripheral injection (Karssen et al., 2003), although it is rapidly cleared. Mifepristone increases the uptake of cortisol into the brain as a result of its effect on the glycogen pump at the blood-brain barrier. Under normal circumstances the glycogen pump hampers the uptake of cortisol; however, mifepristone and its metabolites inhibit the efflux of cortisol via this pump which facilitates the uptake of cortisol into the brain (Sarkar, 2002). Cortisol exerts its effects through two types of receptors in the brain: glucocorticoid receptors and mineralocorticoid receptors (MR). The balance of MR/GR-mediated actions is critical to homeostatic processes in the brain; an imbalance is associated with HPA axis dysregulation (De Kloet and Derijk, 2004). The marked increase in cortisol in the brain following mifepristone administration, together with GR blockade, leads to increased activation of MRs (De Kloet et al., 1998). The attendant shift in balance of MR/GR occupancy is hypothesized to recalibrate the HPA axis by normalizing hormonal set points (De Kloet et al., 1998; Belanoff et al., 2002; Buckley et al., 2008). In PTSD, enhanced central glucocorticoid signaling and normalization of HPA axis regulation could constrain stress responsive systems that are disrupted in PTSD leading to clinical improvement.

To date there are no published studies supporting the use of mifepristone in PTSD, but there is powerful evidence that glucocorticoid manipulation can have therapeutic effects in traumatic stress ([name], 2009). In a study of the treatment of septic shock, it was discovered that ICU patients who received high doses of glucocorticoid were less likely to develop PTSD than those who had not; subsequent randomized controlled trials have confirmed that high dose steroids prevent the development of PTSD in critically ill and surgical patients (Schelling et al., 2004; Schelling et al., 2006). In these patients, high doses of hydrocortisone are hypothesized to work by enhancing glucocorticoid signaling impaired by critical illness. The apparent mechanisms involve down regulation of the stress response, inhibition of traumatic memory retrieval, and facilitation of extinction of aversive information (Schelling et al., 2006). In a small pilot crossover study of low-dose cortisol in PTSD, cortisol was associated with significant reduction in PTSD symptoms (Aerni et al., 2004). The idea of using steroids for PTSD prophylaxis is an intriguing one, but we do not propose hormone replacement as a treatment for chronic PTSD owing to the established adverse effect profile of glucocorticoids when administered at high doses or over long periods of time and because hormone replacement at low doses does not serve to recalibrate the HPA axis in the way that mifepristone is hypothesized to do.

There are data that suggest short-term administration of high doses of mifepristone has beneficial clinical and neuroendocrine effects in other neuropsychiatric conditions which persist beyond the period of medication discontinuation (Belanoff et al., 2002; Young et al., 2004; Gallagher et al., 2005; DeBattista et al., 2006). We also have striking pilot data in a small number of veterans with PTSD that suggests that mifepristone treatment may be efficacious; as such, further study into whether and how this drug can be developed for use in PTSD is warranted. In the absence of published data in PTSD and in the presence of

abundant safety data in other conditions, an exploratory trial for efficacy is the next logical step in developing this drug for use in veterans with PTSD. This study is designed for that purpose.

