### 1.d.3. Descriptive Outcomes

The impact of mifepristone on other clinical parameters will be described, including the three PTSD symptom sub-scales from the CAPS (intrusion/re-experiencing, avoidance/emotional numbing, and hyperarousal), depression (Beck Depression Inventory (BDI)), PTSD (PTSD Checklist (PCL)), sleep quality (Pittsburgh Sleep Quality Index (PSQI)), anger (State-Trait Anger Expression Inventory (STAXI)) and functional impairment (functional impairment measure (item 24) on the CAPS). The neuroendocrine effect of mifepristone in PTSD will be assessed by measuring the changes in plasma cortisol and ACTH levels from baseline to immediately after one week of treatment and from baseline to four weeks. The relationship of plasma cortisol and ACTH levels to clinical response will also be explored. As an additional descriptive measure, plasma levels of mifepristone and its metabolites will be assessed immediately after one week of treatment, and its relationship to clinical response and the trajectories of CAPS scores will be assessed.

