##### 4.n.2. *Sample size determination*

As mentioned above, the sample size has been calculated to provide at least 90% probability that mifepristone 600 mg has been correctly identified as being superior to placebo if the population difference in response rate is at least 15%. Using the calculations provided by Simon et al. (1985) and accounting for a 20% attrition rate which has been reported in other drug studies using a similar population (Bartzokis et al., 2005), a total sample size of 90 is required, or 45 per treatment group. Since the sample size varies according to the responder rate (as well as the magnitude of the difference of interest), and the responder rate for placebo is unknown, we assume a placebo responder rate of 40%, which is at the high end of the studies referenced above. By contrast, in order to have a one-sided Type I error rate of 5% and 80% power to detect the 15% difference between two

groups using a traditional hypothesis testing framework, the study would require 274~344 participants when the placebo responder rate changes from 20% to 44%, after adjustment for a 20% withdrawal rate. If the true population difference in response rate is smaller than 15% (between 10~12%) and if we still consider it clinical significant, the proposed sample size (n=72 completers or 90 with 20% withdrawal rate) will still provide at least 80~85% probability of correctly identifying the superior group.

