- a. Descriptive statistics for the change in score from baseline to one month on the STAXI and confidence intervals will be provided for each treatment group.
- b. Change in score from baseline to one month on the STAXI will be compared between mifepristone and placebo using two-sample t-test (or Wilcoxon rank-sum test if the normality assumption does not hold).
6. Functional Impairment
- a. Descriptive statistics for the change in score from baseline to one month on the functional impairment measure (item 24) from the CAPS and confidence intervals will be provided for each treatment group.
- b. Change in score from baseline to one month on the functional impairment measure (item 24) from the CAPS will be compared between mifepristone and placebo using two-sample t-test (or Wilcoxon rank-sum test if the normality assumption does not hold).
7. Neuroendocrine
- a. Descriptive statistics for the change in score from baseline to one week following treatment, and baseline to one month and confidence intervals for plasma cortisol and ACTH levels will be provided for each treatment group.
- b. Change in plasma cortisol and ACTH levels from baseline to one week following treatment and baseline to one month will be compared between mifepristone and placebo using two-sample t-test (or Wilcoxon rank-sum test if the normality assumption does not hold).
- c. Mean plasma cortisol levels at one month will be compared between clinical responders (30% reduction in CAPS score) and non-responders using a t-test (or Wilcoxon rank-sum test if the normality assumption does not hold). This analysis will be limited to those on mifepristone only.
- d. Mean ACTH levels at one month will be compared between clinical responders (30% reduction in CAPS score) and non-responders using a t-test (or Wilcoxon rank-sum test if the normality assumption does not hold). This analysis will be limited to those on mifepristone only.
8. Mifepristone and its metabolites
- a. Descriptive statistics and confidence intervals for one week following treatment for plasma levels of mifepristone and its metabolites will be provided.
- b. Mean plasma levels of mifepristone and its metabolites at one week will also be compared between clinical responders (30% reduction in CAPS score) and non-responders using a t-test (or Wilcoxon rank-sum test if the normality assumption does not hold).

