- c. A continuous mixed-effects model for longitudinal observations of CAPS scores will also be used adjusting for aforementioned baseline characteristics, indicator variable that contrasts

mifepristone vs. placebo, and plasma levels of mifepristone and its metabolites at one week to determine the effect of them on CAPS scores trajectories.

Although it is not listed as an outcome, the percentage of unique participants with concurrent psychotropic medication use change by 1 month and by 3 month (end of the trial) will be compared between mifepristone and placebo using chi-square tests. Concurrent psychotropic medication change is defined as seeking a rescue medication for those who are not on concurrent psychotropic medication prior to randomization, or seek a new psychotropic medication or require a dose increase for those on a stabilized regimen treating PTSD prior to randomization. Those analyses will also be based on mITT principle. Except the primary analysis of the primary outcome, all efficacy and safety analyses will be performed with a significance level of 5% for two-sided tests. Due to exploratory nature of the study, and the sample size was not powered on hypothesis testing framework, careful consideration is necessary when interpreting the significance of these results on the primary, secondary and descriptive outcomes. The results of the trial are considered to be hypothesis generating and are not to obtain definitive efficacy information. No adjustments for multiplicity on various secondary outcome measures are planned in this phase IIa trial. The lack of adjustment will be noted in the resulting manuscripts.

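### The one-month cortisol and ACTH comparison (item 7b) wastes baseline information and cannot tell normalization of set points from a uniform shift

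*Protocol*

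**What the plan says.** Section 1.a states the mechanism as "The attendant shift in balance of MR/GR occupancy is hypothesized to recalibrate the HPA axis by normalizing hormonal set points", and section 2.a.1 repeats it. Section 1.a also notes, in passing, "Since low cortisol is not an invariable feature of the disorder".

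Section 1.d.3 says how the effect on hormones will be examined: "The neuroendocrine effect of mifepristone in PTSD will be assessed by measuring the changes in plasma cortisol and ACTH levels", from baseline to the end of the treatment week and to four weeks. Item 7b in section 4.p.1 gives the analysis: "Change in plasma cortisol and ACTH levels from baseline to one week following treatment and baseline to one month will be compared", and the values "will be compared between mifepristone and placebo using two-sample t-test (or Wilcoxon rank-sum test if the normality assumption does not hold"). The level is set generally: "all efficacy and safety analyses will be performed with a significance level of 5% for two-sided tests".

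The neighbouring items do not add a randomized contrast of another kind. Item 7a describes change within each arm with confidence intervals. Items 7c and 7d compare one-month levels between responders and non-responders among men on mifepristone only.

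**The concern.** The week-1 and one-month comparisons ask different things. At week 1 the drug is acting and a rise in cortisol and ACTH is expected, so a comparison of mean change fits. At one month the drug has been stopped for three weeks, and the question raised by the rationale is whether hormone levels have settled nearer to normal. A test on change scores answers only whether the average moved.

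Two things follow. First, if there is a net shift, a change score estimates it less precisely than an analysis that adjusts for the baseline value, because it forces the baseline coefficient to be one. Second, the result cannot be read in terms of normalization. A significant difference could be a uniform shift. A null could mean no effect, or movement towards normal from both sides. The sign does not settle it either: section 2.a.1 reads a fall in cortisol at day 21 in other disorders as a sign of normalization, whereas section 1.a describes cortisol in PTSD as often low, where normalization would be a rise.

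At stake is what the trial can say about its own mechanism. The efficacy decision is not at stake.

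**Working it through.** **Inputs from the protocol.** Section 4.n.2 gives "n=72 completers or 90 with 20% withdrawal rate", hence 36 per arm. Item 7b is two-sided at 5%. Table 1 in section 3 gives pilot baseline cortisol of 13.15 (SD 3.52) and 12.43 (SD 6.16) µg/dL with four men per arm. The pooled SD is √((3.52² + 6.16²)/2) = 5.02.

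**Check of the plan's own figure.** The plan states no power for cortisol or ACTH. Its only design figure is the selection probability, with "we assume a placebo responder rate of 40" per cent against 55%. With 36 per arm, P(X₁ > X₂) + ½P(tie) = 0.8786 + ½ × 0.0413 = 0.899, which agrees with the stated 90%. So 36 per arm is a fair basis for what follows.

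**Assumptions, not in the documents.** Let r be the share of variance that lies between patients (equal to the placebo within-patient correlation), d the distance of the group mean from a normal value, and f the fraction of each man's persistent deviation that mifepristone closes. The total SD σ is about 5.

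**Step 1: a pure mean shift.** With an SD of change of 5, the standard error is 5 × √(2/36) = 1.18. Shifts of 1, 2, 3 and 4 µg/dL give power of 13%, 40%, 72% and 92%.

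**Step 2: normalization.** The mean effect is f × d, which is zero when d = 0 however strong the normalization. The baseline slope is r on placebo and (1 − f)r on mifepristone, so the slope difference is f × r whatever d is. Simulated power with full normalization (f = 1, 2,000 runs per case):

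| r | d (µg/dL) | t-test on change | arm-by-baseline |
|---|---|---|---|
| 0.3 | 0 | 5% | 28% |
| 0.3 | 2 | 28% | 27% |
| 0.3 | 3 | 53% | 27% |
| 0.3 | 5 | 91% | 27% |
| 0.5 | 0 | 5% | 71% |
| 0.5 | 2 | 33% | 71% |
| 0.5 | 3 | 60% | 73% |
| 0.5 | 5 | 96% | 74% |
| 0.7 | 0 | 5% | 99% |
| 0.7 | 2 | 42% | 99% |
| 0.7 | 5 | 99% | 99% |

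With half normalization (f = 0.5) and r = 0.5, the t-test has about 5%, 13% and 53% at d = 0, 2 and 5, and the slope contrast 22% to 26% throughout. Neither test is uniformly better: the t-test overtakes the slope contrast when d is large or r is low. The Wilcoxon test tracked the t-test closely in all cases.

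**Step 3: precision lost on the mean comparison.** Take σ = 5, r = 0.5, f = 0.75, d = 2, so the shift is 1.5.
- Change score: the variance is 2(1 − r)σ² = 25.0 on placebo and 25.0 + f²rσ² = 32.0 on mifepristone, average 28.5. The standard error is √(28.5 × 2/36) = 1.26, and 1.5/1.26 = 1.19.
- Baseline-adjusted, common slope (0.5 + 0.125)/2 = 0.3125: the residual variance is 19.6 on placebo and 13.8 on mifepristone, average 16.7. The standard error is √(16.7 × 2/36) = 0.96, and 1.5/0.96 = 1.56.

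Simulated power in this case is 22% for the change score and 34% for the adjusted arm effect. Across r from 0.3 to 0.8, the adjusted arm effect had the higher power at every non-zero d.

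**The case against.** The strongest reply is that the protocol does not describe deviations on both sides of normal. Section 1.a speaks of cortisol that is often low, in the absence of hypercortisolism, and section 2.a.2.a says basal levels are not typically raised and are sometimes low. On that picture normalization leaves a net, if diluted, upward shift, which item 7b does test. Section 2.a.1 itself treats a group-level change as evidence of normalization. The pilot is no help: cortisol SD from baseline to week 4 went from 3.52 to 4.27 on drug and from 6.16 to 2.91 on placebo, with four men in each arm. Cortisol and ACTH are descriptive outcomes, section 4.p.1 calls the results hypothesis-generating, and it warns against reading non-significance as absence of clinical effect.

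Most of this stands, and it limits the point. A reader might infer that the stated hypothesis concerns set points that differ between patients and that item 7b would largely miss it. The documents do not support that. The sentence on set points names neither direction nor variation between patients, and the remark that low cortisol is not invariable does not say that some men run high. The loss of power depends on values the protocol does not give.

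Two things survive the reply. The caution about non-significance rests on small sample size, and a larger sample would not make a location test distinguish normalization from a uniform shift. And the gain from baseline adjustment is largest for just the one-sided shift that the reply supposes. The picture is also not wholly one-sided: exclusion criterion 5a removes men with the lowest screening cortisol, who would contribute most to a net rise.

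**Conclusion.** The point holds as a limited weakness of analysis choice. For the one-month comparison, item 7b discards precision available from the collected baseline, and its result, null or significant, says little about normalization as such. It may miss normalization if deviations lie on both sides of normal, which is an assumption.

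The size cannot be fixed from the documents. Power of the change-score test ranges from about 5% to above 90% over mean distances of 0 to 5 µg/dL. The gain from adjustment (22% to 34% in the case worked) rests on an SD of 5 taken from eight pilot patients, and on assumed correlation and extent of normalization. A slope contrast is informative only if much of the hormone variance lies between patients: with r = 0.3 its power is about 27% even under full normalization. The week-1 comparison, the primary outcome, the sample size and the Phase III decision are not affected.

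**What to change.** Leave the week-1 comparison of change as it is. For the one-month part of item 7b, replace the test on change with a regression of the week-4 cortisol value, and separately ACTH, on arm and centred baseline (log scale if skewed), then add the arm-by-baseline product. Report:

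- the baseline-adjusted arm effect with its confidence interval, as the mean comparison. Take it from the fit without the product, since otherwise its standard error treats the sample mean of baseline as fixed;
- the baseline slope in each arm, and their difference, with confidence intervals, as an exploratory description of normalization. A flatter slope on mifepristone than on placebo is the pattern expected, and the placebo slope accounts for regression to the mean.

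The cost is a few lines of analysis text; Table 2 already schedules both hormones at baseline and week 4. The drawback is that the slope contrast is imprecise if within-patient correlation is low, so it should be presented as descriptive and hypothesis-generating, like the other outcomes in that section.
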